### Quality control

For gram stain, on each slide, a control area for *Staph aureus* (*staphylococcus aureus*) (ATCC25923) and *E. coli* (*escherichia coli*) (ATCC25922) is put as a staining control. For CBNAAT, each test kit includes an inbuilt SPC, an SAC and a PCC. External controls (one positive and one negative) will be used in accordance with local, state accrediting organisations, as applicable.

### Kit verification

As the Cepheid kits to be used for the study for CT/NG are Food and Drug Administration (FDA) approved while that for TV is research use only, a kit verification procedure is planned to evaluate the performance of the GeneXpert platform. A verification panel comprising of 17 samples containing known CT, NG and TV of high, medium and low concentration will be tested on GeneXpert using the recommended kits. The results will be compiled and reviewed to determine the suitability of the platform and the kits for diagnosis of STI in the study.

### Management of RTI/STIs

Women with signs and symptoms of RTI/STIs will be treated based on the syndromic approach as recommended in the national guidelines.^11^ Their partners will be notified and provided necessary treatment. The laboratory reports will be reviewed by the study gynaecologists and delivered to their homes with advice to revisit if needed. Asymptomatic women who need further treatment will be invited to the study clinic for an appointment with the study gynaecologists and to receive medicines. Women will also be provided information and counselled on prevention of STI/RTI. Women requiring admission or additional management will be referred to the collaborating hospital. A complete course of treatment and supply of condoms will be provided for free.

### Statistical analysis and outcome measures

Descriptive and inferential statistical analysis will be performed. Simple proportions and 95% confidence bounds will be calculated to determine prevalence for overall laboratory confirmed RTI/STI and individual microorganism by binomial exact method. We will use a method of purposeful selection of covariates to identify variables for the multivariable models.^23 24^ In the multivariable models, we will include the variables that will change the OR of the outcome variables by 20% from the univariable models. We will present the adjusted models, including variables that will be identified in the procedure. We will assess whether any of the demographic, behavioural, sexual and clinical risk factors are modifying the association between laboratory conformed RTI/STI and any of the abovementioned variables on a multiplicative scale. Computation of sensitivity, specificity, predictive values and likelihood ratios will be derived in diagnosing vaginal infection (TV, BV) and cervical infection (NG, CT) using NAAT as the gold standard of diagnosis compared with syndromic approach which is informed by the presence of symptoms and signs. Analysis will be done using STATA V.16.0 (StataCorp).

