## Methods

### Aims and objectives

The overall aim of the study is to generate information and data related to RTI/STIs among women in India. More specifically, there are three objectives. First, to determine the prevalence of NG, CT, TV, BV and *Candida albicans* (CA) among women residing in the peri-urban and urban mid to low socioeconomic areas of South Delhi at least 14 days after they exit from Women and Infants Integrated Interventions for Growth Study (WINGS). Second, to assess the diagnostic validity of the current RTI/STI syndromic case management practice relative to the aetiologic diagnosis based on laboratory confirmation of NG, CT, TV, BV and CA among symptomatic and asymptomatic women. Third, to identify demographic, behavioural, sexual and clinical factors associated with laboratory confirmed RTI/STI among women. Similar data on syphilis are already being collected as a part of WINGS.^17^

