### Sample collection, storage and transportation

Two swabs will be collected, one vaginal and other endocervical, by the study gynaecologist. The vaginal walls and cervix will be visualised using self-retaining sterile Cusco’s speculum. Vaginal swab specimen will be collected from the posterior fornix and the lateral walls of the vagina for detection of BV and CA and kept in a pre-labelled dry collection tube. Following this, the endocervical swab from the test kit will be inserted gently into the endocervical canal, rotated and withdrawn and kept in the pre-labelled transport reagent container for nucleic acid amplification test (NAAT) for CT, NG and TV.

All samples will be stored at 2°C–8°C in the laboratory and transportation to the testing laboratory will be done daily, in cool boxes maintained at 2°C–8°C.

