### Laboratory procedures

NAAT, a real-time PCR having the highest specificity and sensitivity (98%–100%) among the available conventional tests, will be used to detect CT, NG and TV.^19^ We will use cartridge based (CB) NAAT Gene Xpert platform which is an automated in vitro diagnostic (IVD) test for qualitative detection and differentiation of DNA of CT, NG and TV and is performed on Cepheid GeneXpert Instrument Systems.^20^ With this we will use the GeneXpert CT/NG Cepheid IVD, and GeneXpert TV Cepheid IVD kits.^21^

The GeneXpert Instrument Systems automate and integrate DNA extraction, amplification and detection of the target sequences in simple or complex samples using reverse transcription (RT-PCR). The systems consist of an instrument connected with a computer, with preloaded software for running tests and viewing and generating results. The systems require single-use disposable cartridges that hold the PCR reagents and host the PCR process.

Reagents for the detection of a Sample Processing Control (SPC), a Sample Adequacy Control (SAC) and a Probe Check Control (PCC) are also included in the cartridge. The SPC is present to control for adequate processing of the target bacteria and to monitor the presence of inhibitors in the PCR.

The SAC reagents detect the presence of a single copy human gene and monitor whether the sample contains human DNA. The PCC verifies reagent rehydration, PCR tube filling in the cartridge probe integrity and dye stability. The primers and probes in the Xpert CT/NG test detect chromosomal sequences in the bacteria. One target is detected for CT (CT1) and two different targets are detected for NG (NG2 and NG4). Both NG targets need to be positive for the Xpert CT/NG test to return a positive NG result. Prepared sample is transferred to the sample chamber of the Gene expert cartridge and loaded on the GeneXpert machine and the test is performed.

Summary and detailed test results are generated by the software in approximately 90 min and are displayed in tabular and graphic formats. Nugent’s scoring criteria using a gram-stained slide is the current gold standard with ~77% specificity and 90% sensitivity will be used to diagnose BV.^22^

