A smear will be prepared, and gram staining done. Microscopic examination will be done to detect clue cells and semi-quantitative evaluation for gram-positive, gram-negative or gram-variable bacterial morphotypes quantified. Women will be categorised as non-BV (Nugent Score 0–3), intermediate (Nugent Score 4–6) or BV (Nugent Score ≥ 7) (table 1).

**Table 1 T1:** Nugent score

Organism morphotype	Number/oil immersion field	Score
Lactobacillus-like (parallel sided, gram-positive rods)	>30	0
	5–30	1
	1–4	2
	<1	3
	0	4
Mobiluncus-like (curved, gram-negative rods)	>5	2
	<1.4	1
	0	0
Gardnerella/bacteroides-like (tiny, gram variable coccobacilli and pleomorphic rods with vacuoles	>30	4
	5–30	3
	1–4	2
	<1	1
	0	0

Total score: 0–3=normal; 4–6=intermediate, repeat test later; 7–10=bacterial vaginosis.

Microscopical examination of the vaginal smear will be done for yeast cells with pseudo hyphae to detect CA.

Complete reports will be generated and sent after 48 hours.

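### Objective 2 includes *Candida albicans* in the laboratory reference, but the accuracy analysis leaves it out, so that part of the objective goes unanswered

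*Protocol article*

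**What the plan says.** Under Aims and objectives, the protocol article sets the second objective as the diagnostic validity of syndromic case management "relative to the aetiologic diagnosis based on laboratory confirmation of NG, CT, TV, BV and CA among symptomatic and asymptomatic women".

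The CA result is planned. Sample collection, storage and transportation provides a vaginal swab "for detection of BV and CA and kept in a pre-labelled dry collection tube", and Laboratory procedures adds: "Microscopical examination of the vaginal smear will be done for yeast cells with pseudo hyphae to detect CA".

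Statistical analysis and outcome measures contains the only description of the accuracy analysis. Sensitivity, specificity, predictive values and likelihood ratios are to be computed "in diagnosing vaginal infection (TV, BV) and cervical infection (NG, CT"). One reference test is then named for both of these targets: "using NAAT as the gold standard of diagnosis compared with syndromic approach which is informed by the presence of symptoms and signs". According to Laboratory procedures, NAAT "will be used to detect CT, NG and TV"; BV is diagnosed by Nugent score.

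The same statistical section estimates prevalence for each individual microorganism, so CA is absent from the accuracy analysis only.

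**The concern.** The objective names five conditions and the analysis names four. The article gives no reason for leaving CA out, no separate accuracy analysis for it, and no rule for women who have CA but neither TV nor BV (CA-only women).

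Two things are at stake. First, one of three objectives is only partly answered. Choosing the reference after the results are known would also leave room for a data-driven choice. Second, the study is meant to inform guidance on vaginal discharge. If CA-only women fall on the reference-negative side of the vaginal table, a woman whose discharge goes with a laboratory finding of CA is recorded as a wrong syndromic diagnosis. Readers would then see a lower PPV without being told how much of the shortfall comes from a condition that the objective counts as a true diagnosis.

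**Working it through.** **Comparing the sections**

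| Condition | In objective 2 | Laboratory method planned | In the accuracy analysis | Detected by the named gold standard (NAAT) |
|---|---|---|---|---|
| NG | yes | NAAT | yes, cervical | yes |
| CT | yes | NAAT | yes, cervical | yes |
| TV | yes | NAAT | yes, vaginal | yes |
| BV | yes | Nugent score | yes, vaginal | no |
| CA | yes | microscopy | no | no |

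This comparison establishes the mismatch without any assumed figure.

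**The plan's own figure.** The article gives no precision or sample size for the accuracy analysis. Its 440 is for prevalence: 1.96² × 0.68 / (0.32 × 0.15²) = 362.8, rounded up to 363, and 363 × 1.2 = 436, close to 440. The point made here does not depend on that number or change it.

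**Formulas for the vaginal target.** Let *a* be the prevalence of TV or BV, *c* that of CA only, and *u* = 1 − *a* − *c*. Let the syndrome-positive rates be *Se* (TV/BV), *s* (CA only) and *f* (none of the three). All syndrome positives: P = *a·Se* + *c·s* + *u·f*.

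- TV/BV target, CA-only women reference-negative: PPV = *a·Se*/P; specificity = 1 − (*c·s* + *u·f*)/(*c* + *u*); sensitivity = *Se*.
- TV/BV/CA target: PPV = (*a·Se* + *c·s*)/P; specificity = 1 − *f*; sensitivity = (*a·Se* + *c·s*)/(*a* + *c*).
- PPV difference = *c·s*/P, which is never negative.
- Specificity difference = *c*(*s* − *f*)/(*c* + *u*), which is positive only if *s* > *f*.
- LR+ = sensitivity/(1 − specificity) under each target, so its direction depends on *s*.

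**Illustration.** None of these inputs is in the documents. Assume *a* = 20%, *c* = 15%, *u* = 65%, *Se* = 60%, *f* = 30%, and vary *s*. Each cell gives the TV/BV target, then the TV/BV/CA target.

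| *s* | P | PPV | Specificity | Sensitivity | LR+ |
|---|---|---|---|---|---|
| 30% | 0.360 | 33.3%, 45.8% | 70.0%, 70.0% | 60%, 47.1% | 2.00, 1.57 |
| 40% | 0.375 | 32.0%, 48.0% | 68.1%, 70.0% | 60%, 51.4% | 1.88, 1.71 |
| 70% | 0.420 | 28.6%, 53.6% | 62.5%, 70.0% | 60%, 64.3% | 1.60, 2.14 |

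For *s* = 70%: P = 0.12 + 0.105 + 0.195 = 0.42; PPV = 0.12/0.42 against 0.225/0.42; specificity = 1 − 0.30/0.80 against 1 − 0.195/0.65.

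The two LR+ values are equal when (0.195 + *x*)(0.12 + *x*) = 0.0504 with *x* = 0.15*s*. This gives *x* = 0.0701 and *s* of about 47%. Below that rate, adding CA lowers LR+; above it, adding CA raises LR+.

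**Range**

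- Keeping *Se* = 60%, *s* = 70% and *f* = 30%: with *a* = 25% and *c* = 7%, PPV is 37% against 49%; with *a* = 15% and *c* = 20%, it is 21% against 54%. The gaps are about 12 and 33 points.
- With *a* = 20%, *Se* = 70%, *f* = 30%, *c* from 5% to 20% and *s* from 50% to 90%: PPV is 0.28 to 0.36 under TV/BV and 0.42 to 0.64 with CA, a gap of 0.06 to 0.36. Specificity is 0.55 to 0.69 against 0.70, a gap of 0.01 to 0.15. If all 440 women had results, about 11 (440 × 0.05 × 0.5) to 79 (440 × 0.20 × 0.9) would move from false to true positive.

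**The case against.** The strongest reply has four parts.

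- **Classification is not stated.** A reader might infer that the protocol counts women with candidiasis as disease-free. It does not say so. CA-only women could be excluded, shown separately or pooled, and a condensed article may leave that to the full protocol or analysis plan. A woman with CA plus TV or BV stays reference-positive in any case. This stands: false-positive status follows from the target as written, and only for CA-only women.
- **PPV for TV/BV is a legitimate quantity.** Widening a target while the syndrome positives stay fixed cannot lower PPV. Much of the gap is therefore a change of target, not the removal of an error. This also stands.
- **The direction is not general.** A reader might infer that the plan biases every measure against the syndromic approach. The article's Introduction says that asymptomatic candidal colonisation can occur in up to 60% of cases, so a syndrome-positive rate near 40% among CA-only women is conceivable. It is a low-end assumption, because 60% is an upper limit and signs also feed the syndrome. At 40%, specificity differs by only 2 points, and LR+ falls from 1.88 to 1.71 when CA is added. This stands.
- **A primary composite is debatable.** Asymptomatic women are enrolled by design, so a primary TV/BV/CA reference would count some carriage as disease. This stands against making the composite primary. It does not stand against reporting CA.

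None of this removes the mismatch. The statistical section lists its targets explicitly and the list disagrees with the objective, so this is a contradiction in the text and not a detail left elsewhere. Carriage might justify a TV/BV-only table, but the article does not offer it as a reason.

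**Conclusion.** The point holds as a disagreement between objective 2 and the only accuracy analysis described: the CA part of the objective is not answered. The gold-standard wording in the same sentence does not fit either, because NAAT covers neither BV nor CA. It may be loose phrasing, but it needs correcting.

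The effect on the vaginal table is conditional. If CA-only women are reference-negative, PPV is lower than under a target that includes CA, by about 6 to 36 points over the assumed ranges. Specificity is lower only if CA-only women are syndrome-positive more often than women with none of the three conditions; over the assumed values the gap is 0 to 15 points. LR+ can go either way, with the change near 47% in the main illustration. These sizes rest wholly on assumed prevalences and syndrome-positive rates. The documents do not support a claim of general bias against the syndromic approach.

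The CA prevalence estimate, the risk-factor objective and the cervical (NG, CT) accuracy targets are not affected. This should be fixed before analysis, but it does not undermine the design.

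**What to change.** In Statistical analysis and outcome measures:

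1. Add CA as its own accuracy target, with microscopy as the reference.
2. In the TV/BV table, show CA-only women as a separate row instead of pooling them with women who have none of the three conditions.
3. Report a TV/BV/CA composite as a supplementary analysis.
4. Replace the single gold standard with one reference per organism: NAAT for NG, CT and TV; Nugent score of 7 or more for BV; microscopy for CA.

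If the investigators prefer not to assess accuracy for CA, the alternative is to remove CA from objective 2 with a stated reason, and still say how CA-only women are classified.

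The cost is a wording change and one or two extra tables. It needs no new specimens and no change to the 440. The downside is that microscopy-positive CA includes some asymptomatic carriage. The report should say so, and the separate row lets readers judge its weight.

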### Patient and public involvement

Participants and the public were not involved in the design of this study. However, study results will be shared with the participants and informed about their aetiological diagnosis and provided appropriate treatment.

### Confidentiality

All data will be de-identified, analysed and aggregated before reporting. Furthermore, data will be stored securely and only reviewed by the immediate research team. The information collected from the study participants will be kept confidential and stored in a locked area which can only be accessed by the study team. The participants will not be identified by his/her name but only by a study number. All study documents will be stored for a period of 5 years after which they will be destroyed. Knowledge from this study will be disseminated through reports given to the ethics review committee, government agencies and publications but none will have the name of the study participants.

### Tokens/compensation

Participants will be provided with a reasonable token (not exceeding US$2) of appreciation, along with free medical examination, treatment for STI/RTI and condoms. Usually this is given to compensate for the time spent on study participation. It is considered reasonable to compensate participants for their time. The amount is not considered large to constitute an undue inducement.

### Gender and social equity considerations

The proposed study addresses the sexual and reproductive rights of women related to RTI/STI and will identify risks and vulnerabilities in relation to RTI/STIs in the study context. By understanding the prevalence of laboratory confirmed RTI/STIs as well as diagnostic validity of syndromic approach, the study will provide useful information to the national programme. It will also assist women to access treatment, including asymptomatic women, which will be useful in addressing inequality to service access. The research questions are focused on women. However, there will be opportunities for sexual partners of women identified with RTI/STI to be notified and subsequently provided with treatment as per syndromic management following laboratory/aetiologic results.

### Community engagement

This study will enrol women who previously participated in WINGS, which has a large component of community participation. Participants will also be contacted at their homes, and local communities will continually be reached and mobilised with the results to enhance uptake of interventions that promote better woman and infant outcomes.

### Research capacity strengthening

It is envisioned that exchange of information related to conduct of research and data analysis will continually take place between WHO and the research partners.

### Dissemination

The result of the study will be presented in scientific conferences and published in appropriate peer-reviewed journals.

## Discussion

This study aims to fill an existing gap related to a lack of epidemiologic information on STIs in India. A recent systematic review of syndromic approach found that there was very limited validation of syndromic approach as well as aetiologic studies globally.^25^ With an ever-changing epidemiology of STIs, there is a need to encourage countries to regularly conduct aetiologic studies of syndromes, to inform national STI case management guidelines.

This study will evaluate the diagnostic validity of RTI/STI syndromic approach among women of reproductive age in India while providing important information related to the prevalence of RTI/STIs and the aetiologies of vaginal discharge syndrome in the study context, where there is insufficient prevalence and aetiologic data. Given the serious consequences of RTI/STIs on women’s health, sexual and social relationships and psychological well-being,^26^ this research will make an important contribution to the understanding and mitigation of RTI/STIs in India. Data on prevalence will be relevant for improving the national STI case management in India, and for planning RTI/STI services for women, in order to reduce maternal and neonatal morbidity and mortality, adverse birth outcomes and the sequelae of these infections. However the generalisability of the findings from this study to wider population may be limited by the fact that women who participate in research studies self-select, and therefore may bias the prevalence results

In context of high volume of specimens, one of the key challenges for this study will be to ensure quality of sample collection, transport and processing which will be mitigated through training and regular monitoring. While important, our primary intention at this point is not to compare RTI/STI prevalence between two groups of women (those who get pregnant and those who do not). This substudy will not collect data related to syphilis since prevalence data on syphilis is already being collected as a part of WINGS.^16^
